### **Study Sponsor**

The funding for this study was derived from the grant awarded by the Global Research Awards for Nicotine Dependence (GRAND) 2017

## 1. Background

Cigarette smoking is one of the leading causes of preventable deaths worldwide (1). A report based on data from the Global Burden of Disease study indicates that in 2015, smoking killed more than 6 million people worldwide resulting in a global loss of 150 million disability adjusted life-years (2). In Australia, in the year 2016 alone, 14,900 Australians died from smoking related illnesses. That is 40 preventable deaths every day (3).

Smoking tobacco causes exposure to thousands of toxic chemicals, 70 of which are known carcinogens that have the potential to damage nearly every organ system in the human body (4). The harmful effects of these toxins are well established and include lung cancer, heart disease, chronic obstructive pulmonary disease, stroke and an exacerbation of various mental health conditions (4). Despite the myriad of healthcare risks associated with cigarette smoking, 14.7% of Australian adults aged 18 years or over smoked daily over a 12-month period in 2014-2015 (5).

An extensive body of research has established that quitting smoking has both immediate as well as long term health benefits, reducing the risk for diseases caused by smoking and improving overall wellbeing. A landmark 50-year follow-up study of 34,000 British male doctors started in 1951 provides the strongest evidence for this (6). Many participants in this cohort quit smoking subsequently thereby providing a natural experiment illustrating the impact the number of years of smoking have on health outcomes (6). Approximately two-thirds of persistent smokers in this study were estimated to have died due to their smoking (6). Among those who quit, the greatest health benefit was seen in those who quit earlier (6). Stopping smoking at the age of 50 years decreased the risk of smoking-related death by 50% and quitting at ages 60, 50, 40 or 30 years resulted in gains of about 3, 6, 9, or 10 years of life expectancy, respectively (6). Unlike complete abstinence, research shows no noticeable improvement in health outcomes and lifespan among smokers who cut down the number of cigarettes smoked each day on a long-term basis (6).

Although the daily smoking rate amongst adults 18 years or over has declined over the past decade in Australia, results of the annual Victorian surveys that monitor smoking status demonstrate a low successful quit rate due to a high rate of relapse (5, 6). These surveys monitor the attempts to quit by current smokers in the past 12 months. The survey reports that 81% of regular smokers attempted to quit in 2010, similar to the proportion reported in 2005 (6). The proportion of regular smokers who had made multiple (three or more) attempts to quit increased from 36% in 1998 to 49% in 2010 (6). Furthermore, the survey reports that approximately 77% of current smokers reported previously attempting to quit with 66% of current smokers being classified as unsuccessful quitters (6).

### 1.1 Rationale for the proposed trial

The development and introduction of pharmacological agents for smoking cessation has provided the much-needed assistance for those trying to quit. Various therapeutic agents are currently available to assist in achieving abstinence and a substantial body of research has demonstrated the effectiveness of such therapies in increasing abstinence rates. The most popular of these agents in Australia is nicotine replacement therapies (NRTs) available in the

form of transdermal patches, chewing gums, lozenges, inhalers, mouth sprays and sublingual tablets (6). Smoking cigarettes releases nicotine, the agent responsible for causing addiction (6). The effects of nicotine in the body are mediated via the nicotinic cholinergic receptors in the brain (7). The  $\alpha 4\beta 2$  receptor subtype in particular is believed to be the principal mediator of nicotine dependence. Stimulation of these ligand-gated ion channels triggers the release of various neurotransmitters in the brain which induce signals of pleasure thus reinforcing self-administration and causing dependence (7). Smoking cessation causes the emergence of withdrawal symptoms due to the reduction in the levels of nicotine in the body (7). These symptoms include but are not limited to: irritability, a depressed mood, anxiety and restlessness (7). NRTs replace some of the nicotine in the bloodstream previously derived from cigarettes but without the many thousands of other chemicals that are also present in cigarettes which are largely responsible for causing smoking-related illnesses (6).

Varenicline (Champix®), is another pharmaceutical agent indicated for use as a smoking cessation aid. It is a prescription-only medicine currently available in Australia and is subsidised via the Pharmaceutical Benefits Scheme (PBS). Varenicline has a dual mechanism of action and exerts its pharmacological effect by acting as a partial agonist at the  $\alpha 4\beta 2$  receptors (8). This reduces the drop in the mesolimbic dopaminergic levels that occurs during smoking cessation thereby relieving withdrawal symptoms (8). In addition to this, varenicline also antagonizes the activity of nicotine on the  $\alpha 4\beta 2$  receptor subtype thereby preventing the release of neurotransmitters such as dopamine in the brain and in doing so reduces feelings of pleasure from a smoking relapse (8).

To date, several studies have evaluated the efficacy and safety of NRTs and varenicline when used as monotherapy for smoking cessation. Current literature suggests that both agents are effective in assisting abstinence (9, 10). This is evident from the results of a systematic review and meta-analysis that evaluated 84 randomised controlled trials on the relative efficacies of the different pharmacological agents on abstinence at 1 year (10). The review reported that all forms of NRT and varenicline monotherapy resulted in higher smoking cessation rates at 1 year compared to controls (NRTs 70 RCTs, OR 1.71, 95% CI, 1.55-1.88,  $P < 0.0001$ , varenicline 4 RCTs, OR 2.96, 95% CI 2.12-4.12,  $P < 0.0001$ ) (10).

While several studies have examined the efficacy of both agents at inducing abstinence as monotherapy, limited information is available on the efficacy and safety of combination treatment. Available evidence to date, has been limited to varenicline in combination with NRT patches, a form of long-acting NRT (9, 11, 12). Long-acting NRT delivers a constant amount of nicotine into the bloodstream over a prolonged period of time. In contrast to this, short-acting NRT (SANRT) such as gums and lozenges are administered on demand for immediate relief of cravings and withdrawal symptoms. The effects of SANRT are short-lived and repeated administration is required. The efficacy and safety of varenicline in combination with short-acting forms of NRT is yet to be known. SANRT has proven to be just as effective as NRT patches as monotherapy in assisting smokers to quit (10). Wu et al has reported a pooled OR of 1.60 for NRT gums (95% CI, 1.60,  $P < 0.0001$ ) and an OR of 1.63 for NRT patches (95% CI 1.41-1.89,  $P < 0.0001$ ) versus control at 1 year (10). Varenicline in combination with SANRT may, therefore, greatly enhance the rates of long-term abstinence. During the first couple of weeks of varenicline treatment patients are able to smoke, however, SANRT may allow patients to better manage their cravings and decrease the need for

smoking during this period. The proposed research project, therefore, aims to evaluate the efficacy and safety of this combination treatment.

Smoking is one of the main causes of conditions that result in hospital admissions. Hospitalisation provides an ideal environment for initiation of smoking cessation interventions. The 'smoke-free' environment enforced in Australian hospitals provides inpatient smokers an opportunity to attempt quitting away from their usual environmental triggers to smoke (13). During this time of increased vulnerability regarding their health, patients may be more motivated to quit and may also be more receptive to smoking cessation interventions and change in behaviour (13). This strategy may, therefore, translate to long-term abstinence that continues post-hospital discharge.

## 2. Aim and Objectives

This study aims to evaluate the effectiveness and safety of the combination of varenicline and NRT lozenges at assisting achievement of abstinence amongst heavy smokers admitted to six 'smoke-free' public hospitals in Australia.

The primary objective of the study is to compare biochemically-verified continuous abstinence in hospitalised smokers treated using varenicline plus NRT lozenge versus varenicline monotherapy.

The secondary objectives of this study are to compare:

- Self-reported 7-day point prevalence abstinence and continuous abstinence in the two treatment arms from 2 weeks to 3, 6 and 12 months after treatment initiation
- CO verified 7-day point prevalence abstinence at 6 and 12 months from treatment initiation for participants who self-report abstinence at these follow-ups
- Self-reported treatment adherence and adverse events to the study medicines at all follow-ups as well as the number of Quitline sessions attended after treatment initiation

## 3. Study Design

A 2-arm randomised controlled trial (RCT) with individual patients as the unit of randomisation will be carried out. Eligible inpatient smokers will be randomly allocated to either of the study groups. The trial conforms to the CONSORT guidelines for parallel group RCTs and will be registered prospectively with the ANZ clinical trials registry.

This trial will be carried out in six 'smoke-free' public hospitals in Australia. The study sites are Barwon Health, Peninsula Health, Eastern Health, Monash Health, Bendigo Health and The Queen Elizabeth hospital.

### 3.1 Inclusion Criteria

Adults aged 18 years or over, admitted to participating hospitals with a history of smoking  $\geq$  10 cigarettes per day on average in the four weeks prior to their hospital admission, interested in quitting smoking, willing to use pharmacotherapy and available for a 6 months follow-up post-discharge and willing/capable to provide signed informed consent will be eligible for the study. This study will not recruit any outpatient smokers. Hospitalisation

provides a great opportunity for initiating smoking cessation interventions, firstly because of the 'smoke free' policies in all study sites facilitating quitting, and secondly due to greater patient receptiveness to smoking cessation messages and interventions at a time of perceived vulnerability to negative health outcomes. Moreover, initiation of smoking cessation medications such as varenicline during hospital stay allows close monitoring of patients for any adverse events.

### 3.2 Exclusion Criteria

Patients who do not meet all of the above inclusion criteria, those who have a terminal illness with an anticipated survival of <6 months, those who have an unstable cardiovascular status (recent myocardial infarction or stroke within the past 3 months) or those with a new diagnosis of a major psychiatric illness (e.g. psychosis) will be excluded from the study. Patients unable to communicate in English and provide written consent will also be excluded due to the potential need to regularly communicate with the investigators during the entire trial period and the lack of funding available for interpreters. Further exclusion criteria for this study are women who are pregnant, breastfeeding or planning to become pregnant in the next 6 months, patients who are current (on the day of hospital admission) users of smoking cessation medications or approaches (i.e. NRT, varenicline, bupropion [Zyban™], clonidine, nortriptyline or electronic nicotine cigarettes), those currently participating in other smoking cessation programs or study, patients who have completed ≥12 weeks course of varenicline in the 12 months prior to their hospitalisation, those who have had intolerable adverse reactions from the use of varenicline or NRTs in the past as well as people who have contraindications for their use (see Appendix A) (including those using medications known to have major interactions with either varenicline or NRT).

### 3.3 Recruitment, Initial Screening and Allocation

A trained Research Assistant (RA) will be employed at each of the six hospitals to coordinate participant recruitment. Ward staff including doctors, nurses, pharmacists and physiotherapists will be informed of the study and asked to refer all patients identified as a current smoker to the RA via the paging service. Coffee vouchers will be given to ward staff for patient referrals to the RA that result in successful recruitment. Eligible patients will also be identified by the RA through active screening of the patients' admission notes. In addition to this, flyers containing study information will be displayed in hospital wards to notify inpatients of the study. Flyers will also contain contact information of the RA at the site so that if interested, patients can discuss the study with them. Upon identification of potential study participants, the RA, in consultation with the treating medical team, will assess the patients' eligibility for the study considering their current health status and any apparent contraindications for the use of varenicline or NRTs (Appendix A). Details of this initial medical screening will be recorded by the RA. The RA will then discuss with the Nurse Unit Manager or ward nurse to assess the appropriateness in approaching the patient for an interview.

The RA will describe the project to the patient and provide a participant information sheet. When the patient has had the study explained to them and an opportunity to have any questions asked, written consent will be sought before the initial interview proceeds. Each participant will be assigned a study number and baseline data will be collected during the initial interview using the baseline data collection form. Participants will then be randomised

(1:1) using a randomisation scheme generated using a computer-generated list. Random block sizes of two and four will be used to reduce the predictability of treatment allocation. Each site will be provided with 64 envelopes containing the group allocation. The clinical trials pharmacist will open the envelopes in a sequential manner when a participant is recruited. The pharmacist will then dispense the study medicines as stated in the envelope ([varenicline and NRT lozenges] or [varenicline and placebo lozenges]) and hand these to the RA along with the envelope. The RA will then hand the medicine to the participant and provide detailed counselling. Participants will not be told whether they are receiving NRT or placebo lozenges.

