#### 3.5.1 Intervention Arm

Participants in the intervention arm will receive varenicline plus NRT (lozenges) for 12 weeks. An additional 12 weeks course of varenicline will be provided (i.e. 24 weeks in total) to those who need further support (to be determined by the staff in charge of delivering the intervention based on participant's nicotine dependence, adherence to treatment, and any adverse events]. NRT lozenges/placebo will also be provided to those needing further support.

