### 3.8 Follow-up Interviews

Five follow-up interviews will be conducted over the entire course of the study: at weeks one and three of treatment initiation and at three-, six- and twelve- months from treatment initiation. The one- and three- week follow up interviews will be done by the RA involved in the participant's recruitment. These follow-ups will be conducted face-to-face for participants who are still inpatients or via telephone for participants who have been discharged. Participants who are uncontactable via telephone will be sent text messages and emails for their follow-ups. Three-, six- and twelve-month follow-up interviews will be conducted via telephone by an independent RA who is blinded to treatment allocation and who was not involved in the participant's recruitment.. A total of ten attempts will be made to contact the participant for follow-up interviews. Participants' next of kin will also be contacted if the RAs are unable to reach the participants directly. If a participant is unable to be contacted beyond this point they will be noted as 'lost to follow-up' and they will be considered as "smokers" according to the Russell Standard. Participants who successfully complete follow-ups at 3, 6 and 12 months will be reimbursed for their time via a gift voucher that will be provided at the 12-month follow-up.

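### The opened allocation envelope goes to the recruiting research assistant, leaving early safety data interviewer-unblinded and the next allocation guessable better than chance

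*Combined protocol and SAP*

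**What the plan says.** Protocol section 3.3 sets out the allocation steps:

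- **List.** Patients are allocated 1:1 from a list made by computer. On blocking, the protocol states: "Random block sizes of two and four will be used to reduce the predictability of treatment allocation". Every hospital holds its own set of 64 allocation envelopes.
- **Opening and dispensing.** "The clinical trials pharmacist will open the envelopes in a sequential manner when a participant is recruited". The pharmacist dispenses the combination named in the envelope, "and hand these to the RA along with the envelope".
- **Handover.** "The RA will then hand the medicine to the participant and provide detailed counselling". Participants are not told which lozenge they have. Nothing is said about resealing or coding the envelope, or about blinding this RA.

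Other sections give the same role further tasks. Section 3.3 places one RA at each hospital to coordinate recruitment, review admission notes, assess eligibility with the treating team and seek consent. Section 3.4 gives the RA and the treating team joint discretion over patients with a cautionary condition. Section 3.8 adds: "The one- and three- week follow up interviews will be done by the RA involved" in recruiting that participant. The subsections on follow-ups 1 and 2 list the content: adherence and adverse effects at week 1; side effects, adherence, withdrawal symptoms, cravings and relapses at week 3.

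Blinding of staff is stated in two settings only: the 3-, 6- and 12-month follow-ups (sections 3.8 to 3.8.5) and the CO test (section 3.9.2). For a further 12 weeks of varenicline, section 3.5.1 leaves the need "to be determined by the staff in charge of delivering the intervention", without saying whether those staff know the allocation.

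**The concern.** The trial uses a placebo lozenge so that the arms are handled alike, but the person with most contact at entry and in the first weeks is given the allocation. Three things are at stake.

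- **Selection at entry.** Someone who knows the past allocations at a site, and who influences who is approached and who is judged suitable, may act on a guess about the next one. Blinded outcome assessment later cannot repair this.
- **Counselling.** Advice on lozenge use and encouragement to quit can differ by arm, without intent.
- **Early ascertainment.** An interviewer who knows the arm may probe or record nicotine-type effects differently. These reports enter the SAP safety comparison, which starts at treatment initiation. SAP Tables 4 and 5 also report week 1 separately. (Their next early time point is headed week 2, whereas the protocol's second interview is at week 3.) Safety of the combination is part of the stated aim.

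The protocol acknowledges that taste and texture may unblind participants (section 3.5), but not this avoidable route. Neither document describes the early data as collected by an unblinded interviewer.

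**Working it through.** The plan gives no figure for predictability, so there is none to reproduce. The question is how well an RA who sees every past allocation at a site could guess the next.

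**Inputs from section 3.3.** Ratio 1:1; block sizes two and four, printed in the protocol; 64 envelopes per site, opened in sequence.

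**Assumptions.** The mix of block sizes is not stated: take half the blocks as size two, with a range of 25% to 75%. Each site's envelopes start on a new block. The RA sees all past site allocations and knows the sizes in use.

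**Step 1: correct guesses.** Every block ends balanced, so the best guess is always the arm that is behind in the site tally, with a coin toss when level. Block boundaries need not be known.

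- Block of two: 0.5 + 1 = 1.5 correct of 2.
- Block of four: first place 0.5; second 2/3; third (1/3 × 1) + (2/3 × 0.5) = 2/3; fourth 1. Total 2.833 of 4.
- Equal mix, mean block length 0.5 × 2 + 0.5 × 4 = 3: (0.5 × 1.5 + 0.5 × 2.833) / 3 = 2.167 / 3 = 72.2%.
- 25% blocks of two: (0.25 × 1.5 + 0.75 × 2.833) / 3.5 = 71.4%.
- 75% blocks of two: (0.75 × 1.5 + 0.25 × 2.833) / 2.5 = 73.3%.

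**Step 2: allocations known with certainty, boundaries unknown.** This happens only when one arm leads by two. The current block must then be a four that opened with two alike, so its last two places are fixed. A block of four opens that way with probability 1/3, giving 2 × 1/3 = 0.667 certain places per block of four.

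- Equal mix: 0.5 × 0.667 / 3 = 11.1%.
- 25% blocks of two: 0.75 × 0.667 / 3.5 = 14.3%.
- 75% blocks of two: 0.25 × 0.667 / 2.5 = 6.7%.

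**Step 3: simulation check.** 4,000 lists of 64 envelopes, with guesses updated by Bayes' rule from the full history:

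| Share of blocks of two | Correct guesses | Certain |
|---|---|---|
| 25% | 71.3% | 14.0% |
| 50% | 72.1% | 10.7% |
| 75% | 73.3% | 6.5% |

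The small differences from steps 1 and 2 come from the finite list and simulation error.

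**Step 4: comparison.** If the RA never sees an allocation, correct guessing is 50% and nothing is certain.

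**The case against.** The strongest reply is that the plan protects what matters most. The 6-month interview is done by an independent blinded RA and the CO test by blinded RAs. Consent and baseline data precede randomisation, and the pharmacist opens the envelopes. Eligibility is assessed with the treating team, and cautionary cases also go to a clinician. Participants are not told their lozenge, so week-1 and week-3 self-reports come from people not told their arm. Serious adverse events go to a committee. The plan never claims that recruiting staff are blinded, so this is a design weakness and not a contradiction.

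Most of this stands, and it limits the point. It does not remove it: the RA still reviews notes, approaches patients and shares some decisions, and ordinary adverse events are not adjudicated.

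A reader might infer several stronger things that the documents do not support:

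- **That random blocks achieve nothing.** The protocol claims only to reduce predictability. For the same observer, fixed blocks of four would make 33% of allocations certain and fixed blocks of two 50%, against about 11% for the mix. About 89% stay uncertain.
- **That larger blocks are needed.** Blocks of 4, 6 and 8 lower correct guessing only to about 68%. Withholding the envelope lowers it to 50%, after which block size adds nothing here.
- **That extended treatment is decided unblinded.** Section 3.5.1 neither names the RA nor says that these staff know the allocation. It lists criteria, and section 3.5.2 offers extension in the comparator arm too. The gap is that blinding is unstated.
- **That bias occurred.** The text shows an opportunity, not an effect.

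**Conclusion.** The point holds as a design weakness that should be fixed. As written, the recruiting RA receives the allocation and then counsels and collects the week-1 and week-3 data, which are interviewer-unblinded while participants are not told their arm. Foresight of the next allocation is about 72% against 50% (71% to 73% over the range of mixes), with about 11% certain (roughly 7% to 14%). These figures rest on the assumed block mix and on an RA who keeps a tally; they measure opportunity, not bias in the treatment estimate. Assessment of the 6-month primary outcome is blinded, so the primary comparison is exposed only through selection at entry and differential handling. The early adverse event comparison is exposed directly.

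**What to change.** **If envelopes remain unopened.** In section 3.3, delete the words that pass the envelope to the RA. The pharmacist keeps each opened envelope in pharmacy and hands over a pack labelled by study number, with the same label form in both arms. State that recruiting RAs, and whoever decides on extended supply, are blinded to allocation. The cost is a small change to pharmacy procedure and labelling, with a minor amendment.

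**If recruitment is complete,** as the past tense of the SAP's sample size section suggests, those changes come too late. State in the SAP and the report that recruiting RAs were unblinded, label week-1 and week-3 outcomes as interviewer-unblinded, and report extended treatment by arm. The cost is a stated limitation on the early safety data and some added reporting.
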